#### Statistical analyses

Qualitative variables will be described using the sample numbers and percentages. Quantitative variables will be described using the mean (+/− standard deviation) or the median and the range if normality hypothesis is not verified*.*

To address the primary objective, the rate of successful PDTO establishment, i.e., the rate of tumor samples usable for predictive functional assays based on PDTO, will be estimated with its 95% confidence interval. Then, PDTO response to treatment will be correlated with the clinical response by performing a Chi2 test and computing the Cohen’s kappa coefficient. Associations between biological parameters and clinical response will be assessed by one-way analysis of variance (or the non-parametric Kruskal-Wallis test, if necessary). Receiver Operating Characteristic (ROC) curves and a logistic regression model will also be used to identify predictive factors of clinical response.

An alpha level of 5% will be considered to indicate statistical significance for each statistical analysis and confidence interval.

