### Study objectives

The main objective of the study is to assess the feasibility of using PDTO from HNSCC as tools for predicting response to treatments.

The secondary objectives are: i) to assess the feasibility of in vitro functional assays for evaluation of sensitivity to treatments (chemotherapy, radiotherapy, PARP inhibitors and immunotherapy); ii) to investigate the predictive value of PDTO for conventional chemotherapy and radiotherapy; iii) to evaluate the PARP inhibitor-mediated sensitization of radiotherapy; iv) to assess the ability of PDTO to repair DNA lesions by homologous recombination [(HRD (Homologous Recombination Deficiency)/HRI (Homologous Recombination Intermediate)/HRP (Homologous Recombination Proficiency) status); v) to identify molecular signatures for prediction of response (of PDTO and patients) to treatments.

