#### Medical data collection

Medical data collected for each patient in order to correlate biological data (including PDTO response to treatment) with clinical response are indicated in Table 2.

**Table 2 Tab2:** Medical data collected for each patient

Clinical parameters	Age, sex, weight, height, ECOG performance status, Exposure to tobacco and alcohol, Cancer location and TNM-8 classification
Histological diagnosis	Type, squamous differentiation, keratinization type, p16 status
Biologic parameters	Serum neutrophils, albumin and leukocytes levels
Pathological pronostic factors	Surgical margin, lymph node metastasis with or without capsular rupture, vascular or lymphatic embolization, perineural invasion
Oncologic treatments	Radiotherapy (volume, dose, fraction) Chemotherapy (molecules, administration regimen)
Response to treatment	Disease-free survival, Progression-free survival, Overall survival.

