#### Evaluation of response to treatments

The evaluation of the response to treatments will be performed when PDTO have reached a diameter of 150 μm in « PDTO treatment medium », corresponding to the PDTO culture medium lacking N-Acetylcysteine, Y-27632 and primocin.

PDTO will be collected, resuspended in 2% extracellular matrix/PDTO culture medium and then platted in white and clear bottom 96-well plates previously coated with a 1:1 volume mix of PDTO treatment medium with extracellular matrix. In the case of evaluation of the response to radiotherapy, PDTO will be before irradiated using the CellRad System (FAXITRON Bioptics). In the case of evaluation of the response to chemotherapy or PARP inhibitors, drugs are prepared in 2% extracellular matrix/PDTO culture medium and added 1 hour after PDTO have been plated.

In the case of evaluation of the response to immunotherapies, PDTO will be co-cultured with PDTO specific T cells previously generated (*see co-culture of PDTO with immune cells*) at a 5:1 ratio. Treatments (such as Nivolumab or Pembrolizumab) will be added directly in the co-culture. A condition containing an MHC-I blocking antibody will be added to control for antigen specific killing.

PDTO morphology will be monitored by taking images during the required time using Incucyte S3 (Sartorius). At the endpoint, PDTO response will be assessed using CellTiter-Glo 3D cell viability assay (Promega) according to the manufacturer’s instruction and luminescence will be measured using GloMax Discover GM3000 (Promega) with the associated software. Results will be normalized to the control condition. IC50 will be calculated with GraphPad software. The ability of T cells to recognize and induce lysis of PDTO will be monitored via analysis of caspase 3 cleavage within PDTO and visualization of LAMP-1 on the membrane of CD8+ T cells.

The treatment response of the PDTO will be finally compared to the clinical response (PFS/DFS/OS) of the patient from whom they are derived in order to validate the predictive value of this model for HNSCC.

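### Clinical response is recorded only as censored survival times, but every method named for analysing it assumes uncensored data, and Chi2 and kappa also require the continuous organoid read-out to be split

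*Protocol article*

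**What the plan says.** **Outcome.** Table 2 (Medical data collection) lists under response to treatment only "Disease-free survival, Progression-free survival, Overall survival". Evaluation of response to treatments repeats this: "The treatment response of the PDTO will be finally compared to the clinical response (PFS/DFS/OS) of the patient from whom they are derived". No tumour-response category or other yes/no outcome is listed.

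**Organoid read-out.** The same section measures viability by luminescence, normalises it to control, and states that "IC50 will be calculated with GraphPad software". Both quantities are continuous.

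**Methods.** Statistical analyses names three sets:
- For organoid against clinical response, Chi2 and kappa: "PDTO response to treatment will be correlated with the clinical response by performing a Chi2 test and computing the" (the statistic named next is kappa).
- For biological markers, a comparison of means with Kruskal-Wallis as the fallback: "Associations between biological parameters and clinical response will be assessed by one-way analysis of variance".
- For prediction, two methods that need a yes/no outcome: "Receiver Operating Characteristic (ROC) curves and a logistic regression model will also be used to identify predictive factors of clinical response".

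No Kaplan-Meier, log-rank, Cox or time-dependent ROC method appears.

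**Follow-up.** Study assessment gives 3 years of enrolment, 5 years of monitoring per patient and 10 years in total. Donors may object at any time, after which data collection stops.

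**Objective served.** Secondary objective ii is "to investigate the predictive value of PDTO for conventional chemotherapy and radiotherapy".

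**The concern.** A survival time is known exactly only for patients who have the event. The others are known to be event-free up to their last contact. All the named methods need a category or a fully observed value, so a patient who withdraws at, say, 18 months must be dropped or counted as event-free. Chi2 and kappa also need the viability or IC50 value reduced to classes such as sensitive and resistant, which discards information in a small data set.

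At stake is the question the article puts forward in its abstract and Discussion: whether organoids predict the patient's outcome. A real association could be missed, and the answer could depend on where the outcome and the read-out are cut.

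**Working it through.** **1. The plan's own figures.** The only sample-size calculation concerns the establishment rate: 60%, 95% interval of total width 20%, 89 samples, 98 patients. The Wilson interval width is 2z·√[p(1−p)/n + z²/(4n²)] / (1 + z²/n). With p = 0.60, z = 1.96 and n = 89:
- p(1−p)/n = 0.24/89 = 0.002697;
- z²/(4n²) = 3.8415/31,684 = 0.000121;
- width = 3.92 × √0.002818 / 1.0432 = 0.1995.

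At n = 88 the width is 0.2006, so 89 reproduces. Then 89 × 1.10 = 97.9, giving 98. These figures do not depend on the present point. No power is stated for the predictive-value analysis, so there is none to reproduce.

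**2. Fit of method to data.**

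| Method | Outcome needed | Organoid or biological measure | Handles censoring? |
|---|---|---|---|
| Chi2, kappa | categories | must be split | no |
| ANOVA, Kruskal-Wallis | groups | stays continuous | no |
| Logistic, ROC | yes/no | stays continuous | no |
| Recorded data | time, censored | continuous | needed |

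**3. Inputs for the size.** From the document:
- Established lines: 0.60 × 89 = 53.4, so 53.
- Background says more than two thirds of operated patients have adjuvant treatment: 53.4 × 2/3 = 35.6, so about 36.
- Background puts relapse at up to half, with no time horizon.

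Assumed:
- 50% events by 5 years, exponential times;
- standard-normal organoid score with hazard ratio 1.8 per SD;
- two-sided 5% test;
- loss to follow-up of 0, 20 or 40%.

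**4. Simulated power** (3,000 runs per row). Logistic and Chi2 use event status, counting lost patients as event-free.

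| n | Loss | Cox, continuous | Logistic, continuous | Log-rank, median split | Chi2, median split |
|---|---|---|---|---|---|
| 53 | 0% | 82% | 78% | 60% | 60% |
| 53 | 20% | 79% | 75% | 59% | 55% |
| 53 | 40% | 75% | 66% | 54% | 48% |
| 36 | 0% | 65% | 61% | 45% | 47% |
| 36 | 40% | 56% | 48% | 36% | 36% |

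The simulation error is about √(0.6 × 0.4/3,000) = 0.9 points. Repeat runs at n = 53 without loss gave 82–84% for Cox, 78–80% for logistic and 60–62% for Chi2. Chi2 is coarse at small n: at n = 35 it gives 39–40%, against 47% at n = 36.

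**5. Splitting the loss into parts (n = 53).**
- Splitting the read-out, Cox minus log-rank: 82 − 60 = 22 points; at 40% loss, 75 − 54 = 21.
- Using status instead of time, log-rank minus Chi2: 60 − 60 = 0; at 40% loss, 54 − 48 = 6.
- Cox minus logistic: 82 − 78 = 4; at 40% loss, 75 − 66 = 9.

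**6. Sensitivity (n = 53, no loss).**
- Hazard ratio 1.5 per SD: Cox 53%, Chi2 36%. Hazard ratio 2.0: 92% and 72%.
- Truly binary organoid response with hazard ratio 2.5: log-rank 64%, Chi2 63%; with 40% loss, 53% and 48%.
- Outcome cut at 2 years instead of 5 (hazard ratio 1.8 per SD): Chi2 falls to about 35%.

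**7. Bias.** With no true effect and loss of 50% in one organoid group against 10% in the other, Chi2 on raw status rejects 11.8% of the time and log-rank 4.9%. At 30% against 10%, Chi2 rejects about 6%.

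**The case against.** The strongest defence is that the plan already contains most of the remedy. Logistic regression and ROC keep the read-out continuous and come within 4 to 9 points of Cox at n = 53. Every patient is to be followed for 5 years, and 3 + 5 = 8 years fits inside the 10-year study, so a common horizon exists and event status at 5 years is a usable outcome. This stands, and it limits the size of the point. It does not remove it: withdrawal with cessation of data collection is foreseen, and the method named specifically for comparing organoid and clinical response is Chi2 with kappa, the least efficient of the set.

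A second defence is that this is a condensed article. Cut-offs, a responder rule, handling of early loss and a lead endpoint may sit in the full protocol or analysis plan. That also stands, so their absence is not counted here. The point rests on methods that are stated and do not fit the recorded outcome.

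Third, the power figures assume proportional hazards and a log-linear effect, which favour Cox. This is fair: with a truly binary organoid response the gap nearly disappears.

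Four stronger readings are tempting but unsupported:
- *Ignoring censoring destroys the power.* It costs about 0 to 6 points here; splitting the read-out costs far more.
- *The results will be biased.* Clear inflation needed strongly unequal loss between organoid groups, and the document gives no loss rates.
- *Every named method forces splits on both sides.* Only Chi2 and kappa do.
- *The primary objective is compromised.* Its wording mentions predicting response, but Statistical analyses ties it to the establishment rate, and the sample size rests on that rate alone.

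**Conclusion.** The point holds in a limited form and should be fixed. The document defines clinical response through three censored times and names only methods that cannot use them as such. The consequence falls on secondary objective ii and the biomarker analyses.

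Under the stated assumptions, Chi2 on a median split has about 60% power at 53 lines, against about 79% for logistic regression and 83% for Cox on the continuous read-out. The hazard ratio, event rate, loss rates and distribution are assumptions, so the ordering and the rough size of the gap matter more than any single figure. The gap is real if organoid sensitivity is graded, and small if it is truly all-or-none.

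**What to change.** In Statistical analyses:

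- **Main analysis of predictive value:** a Cox model of disease-free survival on the continuous read-out (for example log IC50 or viability), with hazard ratio and 95% confidence interval, and Kaplan-Meier curves by read-out group. Overall survival is supportive. Disease-free survival suits a population that all undergo surgery.
- **Population:** patients who received the treatment that was tested on their organoids. Without this restriction the model tests prognosis rather than objective ii.
- **Biological parameters:** Cox models in place of ANOVA or Kruskal-Wallis.
- **Discrimination:** a C-index, or time-dependent ROC at a fixed horizon, in place of ordinary ROC and logistic regression.
- **Supportive only:** Chi2 and kappa, or a 2×2 table with sensitivity, specificity and predictive values with confidence intervals, at a pre-specified time point and cut-off and with a rule for patients censored earlier.

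The wording should be settled before organoid results are linked to outcomes. No extra patients are needed, and no new outcome beyond those in Table 2. The costs are somewhat more analysis work and a proportional-hazards assumption to check. With about 53 × 0.5 ≈ 26 events at most, the models must stay small. In about 36 adjuvantly treated patients even Cox reaches only about 65% power under these assumptions, so the estimate and its interval should carry the conclusion.

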### PDTO could predict the response of the tumor

More and more evidence indicate that PDTO may predict the response of the tumor from which they are derived [7]. A pilot study showed that PDTO from metastatic gastrointestinal tumors predicted the response of 21 patients to different chemotherapies (100% sensitivity, 93% specificity, 88% positive predictive value and 100% negative predictive value) [13]. Another study using PDTO from 11 chemo-naive pancreatic tumors gave a 91% predictive response rate to first-line chemotherapy and 80% to second line chemotherapy [14].

The predictive value of tumor PDTO is also observed for radiotherapy. In their study analyzing 19 patients suffering from colorectal cancer, Park et al. were able to develop a model to predict radio-sensitivity (82% accuracy) and radioresistance (93% accuracy) of patients [15]. Moreover, Driehuis et al. showed that PDTO derived from patients with the worst progression-free survival for HNSCC were more likely to be resistant to radiotherapy [8]. Finally, the response to a combination of chemotherapy and radiotherapy could be efficiently predicted (84% accuracy) using PDTO from colorectal cancer [16]. Altogether, these data highlight the predictive value of PDTO and the relevance to use them to anticipate the response to radiotherapy and its combinations with other treatments. Since the tumor microenvironment also play a critical role in dictating the response to therapies, more and more work is done to complexify the culture of PDTO in order to faithfully recapitulate it. Several trials to culture PDTO with fibroblasts, macrophages or T cells have thus been conducted [17] and gave rise to complex in vitro models. Some of them were used to evaluate the response to immunotherapy in PDTOs derived from melanoma [18] or appendicular cancers [19] and displayed a promising correlation with the clinical response (85 and 100% accuracy respectively). More evidence is still needed to conclude and several trials are currently running to evaluate the predictive value of PDTO in a clinical context [6].

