If the predictive value of PDTO model is validated, this would allow testing conventional treatments before administering them to the patient from whom the PDTO are derived. This perspective is very interesting, particularly in HNSCC where more than two thirds of the operated patients will undergo adjuvant treatments such as radiotherapy and/or chemotherapy whose side effects can be important. Despite these treatments, up to half of patients will relapse, highlighting the radio-chemosensitivity heterogeneity of tumors [20]. A predictive screening using PDTO could thus help to refine the choice of treatments adapted to each patient and thus limit adverse effects. As immunotherapies are increasingly considered to treat HNSCC, the development of PDTO models capable to i) assess the efficacy of such treatment and ii) predict patients’ response to these new agents; will be critical in the next few years. In this regard, our study will allow a first set of functional assays in PDTO co-cultured with autologous immune cells and will give initial pieces of evidence about the efficacy of immunotherapies in HNSCC.

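### The only summaries explicitly assigned to PDTO against clinical response, a Chi2 test and kappa, do not report predictive value and do not separate false-resistant from false-sensitive calls

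*Protocol article*

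**What the plan says.** *Study objectives* lists as secondary objective ii "to investigate the predictive value of PDTO for conventional chemotherapy and radiotherapy". *Evaluation of response to treatments* sets the PDTO result against the "clinical response (PFS/DFS/OS) of the patient from whom they are derived in order to validate the predictive value of this model for HNSCC".

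The analysis is in *Statistical analyses*: "PDTO response to treatment will be correlated with the clinical response by performing a Chi2 test and computing" Cohen's kappa. The same paragraph adds: "Receiver Operating Characteristic (ROC) curves and a logistic regression model will also be used to identify predictive factors of clinical response". It does not say whether PDTO response is one of those factors. Sensitivity, specificity, PPV and NPV are not named as outputs.

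Two parts of the Background section *PDTO could predict the response of the tumor* bear on this. The first precedent it cites, a pilot series of 21 patients with metastatic gastrointestinal tumours, is reported as "100% sensitivity, 93% specificity, 88% positive predictive value and 100% negative predictive value". The hoped-for use is to "refine the choice of treatments adapted to each patient and thus limit adverse effects".

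**The concern.** A predictive value answers a conditional question: given what the assay says, how likely is the outcome? Chi2 tests whether assay and outcome are associated. Kappa measures agreement beyond chance and treats assay and outcome as two interchangeable raters. Neither answers the question that objective ii asks.

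The two errors also mean different things for a tool meant to guide treatment choice. A false-resistant call argues against a treatment after which the patient did not relapse. A false-sensitive call supports a treatment after which the patient did. A summary that pools them cannot show which kind of assay the study has produced, and it cannot be set beside the four measures reported by the first cited series.

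**Working it through.** **Inputs.** The article gives no target figure for objective ii. Its 89 samples and 98 patients (*Sample size determination*) serve the establishment rate. The 89 is reproduced by a Wilson interval at 60% (width 0.1995), but it matters here only for the likely number of lines: 0.60 × 89 = 53.4, taken as 54. The relapse rate is taken from "Despite these treatments, up to half of patients will relapse", so 27 of 54 is the upper end. Error counts are assumed. A positive call means resistant, and the event is relapse.

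**Formulas.** With a = resistant/relapse, b = resistant/no relapse, c = sensitive/relapse, d = sensitive/no relapse:
- Chi2 = N(ad − bc)² / [(a+b)(c+d)(a+c)(b+d)], uncorrected
- kappa = (po − pe)/(1 − pe), with po = (a+d)/N and pe = [(a+b)(a+c) + (c+d)(b+d)]/N²
- PPV = a/(a+b); NPV = d/(c+d); false-resistant rate = b/(b+d)

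**At 50% relapse.**

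| | a, b, c, d | kappa | Chi2 | PPV | NPV | False-resistant |
|---|---|---|---|---|---|---|
| Assay A | 27, 13, 0, 14 | 0.52 | 18.9 | 27/40 = 68% | 14/14 = 100% | 13/27 = 48% |
| Assay B | 14, 0, 13, 27 | 0.52 | 18.9 | 14/14 = 100% | 27/40 = 68% | 0/27 = 0% |

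For both, po = 41/54 = 0.759 and pe = 0.5, so kappa = 0.259/0.5 = 0.52. For both, Chi2 = 54 × 378² / (40 × 14 × 27 × 27) = 18.9. The reason is general: when half the patients relapse, pe is 0.5 however the calls fall, so kappa = 2po − 1 and depends only on the total number of errors.

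The extreme split is not needed. If two thirds of the lines come from patients given adjuvant treatment (53.4 × 2/3 = 35.6, taken as 36, with 18 relapses), tables (17, 8, 1, 10) and (10, 1, 8, 17) both give kappa 0.50 and Chi2 10.6. PPV is 68% against 91%, and NPV is 91% against 68%.

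**Away from 50%, with 54 patients.**
- Same error counts, swapped, with 18 relapses: 12 false-resistant and 2 false-sensitive calls give kappa 0.49; 2 and 12 give 0.32. False-resistant rates are 12/36 = 33% and 2/36 = 6%.
- Same error rates, swapped (sensitivity/specificity 100%/52% against 52%/100%): at 40% relapse kappa is 0.46 against 0.56 and Chi2 16.3 against 21.2; at 30%, kappa is 0.39 against 0.60 and Chi2 13.2 against 23.2.

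In the first case the assay with more false-resistant calls has the higher kappa; in the second it has the lower. The statistics now differ, but their values do not tell the reader which error occurred.

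**Dependence on relapse rate.** With sensitivity and specificity both 85%, kappa is 0.70, 0.60 and 0.46 at 50%, 20% and 10% relapse. PPV moves too: 85%, 59% and 39%.

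**The case against.** Much of the case on the other side stands, and it limits the point.

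- *Special case.* A reader might infer that Chi2 and kappa always give the same answer for opposite errors. They do not. In the same patients, equality needs 50% relapse, and the article gives that only as an upper limit.
- *Direction.* A reader might also infer that an assay that predicts the wrong way would pass unnoticed. Chi2 alone would miss it, but kappa is signed: reversing every call in Assay A gives −0.52 with Chi2 still 18.9.
- *ROC and logistic regression.* These are planned, and PDTO response is an obvious candidate predictor. If it is included, sensitivity and specificity can be read off the curve, and the false-resistant rate is 1 minus specificity. The text neither includes nor excludes it, and a ROC curve alone does not give PPV or NPV.
- *The table itself.* Chi2 and kappa both need the 2x2 table, and the article describes qualitative variables by numbers and percentages. If the table is published, a reader can derive all four measures. It would go too far to say that objective ii cannot be answered.
- *Prevalence.* Moving with the relapse rate is no argument against kappa in particular, since PPV and NPV do the same.
- *Precedents.* Only the first cited series is given with all four measures. Several others are reported as accuracy, which is overall agreement.
- *Status.* Objective ii is secondary, its use in treatment choice lies in the future, and a full protocol or SAP may list more measures.

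The last argument does not remove the point. The article does not merely stay silent: it names the measures for this comparison, and those measures do not match the objective.

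**Conclusion.** The point holds in a limited form. The measures explicitly assigned to PDTO against clinical response are an association test and an agreement index. Neither is a predictive value, and both pool false-resistant with false-sensitive calls. At 50% relapse the masking can be complete: kappa 0.52 and Chi2 18.9 for two assays whose false-resistant rates are 48% and 0%. At lower relapse rates the statistics separate, but without showing which error dominates.

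The illustration assumes 54 evaluable patients, 27 relapses, a two-way classification of both results, and chosen error counts. The mismatch between measures and objective does not depend on those numbers. The documents do not support saying that objective ii is unanswerable or that the planned statistics are computed wrongly. This is a change that should be made to a secondary analysis central to the study's rationale; the primary objective is unaffected.

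**What to change.** In *Statistical analyses*:

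1. Make sensitivity, specificity, PPV and NPV of the PDTO call, each with an exact 95% CI, the main summaries for objective ii, taken from the same 2x2 table. If PFS, DFS or OS are analysed as times, use the time-dependent equivalents.
2. Report both error rates: patients without relapse called resistant, and patients with relapse called sensitive.
3. Keep Chi2 and kappa as descriptive.
4. State whether the ROC and logistic regression analysis includes PDTO response.

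The cost is wording, with no new data. There are two downsides. The intervals will be wide: 14 of 17 gives an exact 95% CI of 57% to 96%, and even 14 of 14 has a lower limit of 0.025^(1/14) = 77%. PPV and NPV will apply to the relapse rate seen in this cohort, and the text should say so.

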### Statistical consideration

#### Sample size determination

To estimate the successful PDTO establishment rate, assumed around 60%, with a 95% confidence interval of 20% width, 89 tumor samples will be required. Anticipating 10% of non-assessable samples, it is planned to include 98 patients.

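### Predictive factors are sought and PDTO prediction assessed in one cohort of about 53 lines, where apparent performance is biased upward, yet the PDTO comparison is said to validate predictive value

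*Protocol article*

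**What the plan says.** The Statistical analyses section sets out two steps beyond the establishment rate.

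- For agreement: "PDTO response to treatment will be correlated with the clinical response by performing a Chi2 test and computing the Cohen’s kappa coefficient".
- For predictors: "Receiver Operating Characteristic (ROC) curves and a logistic regression model will also be used to identify predictive factors of clinical response".

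Both use the same level: "An alpha level of 5% will be considered to indicate statistical significance for each statistical analysis and confidence interval".

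The section on evaluation of response to treatments describes viability normalised to control and an IC50, which are continuous readouts. It gives no threshold between sensitive and resistant. It then compares PDTO response with PFS, DFS and OS "in order to validate the predictive value of this model for HNSCC". The secondary objectives are worded more softly: they speak of investigating predictive value and identifying signatures.

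Table 2 lists the clinical candidates collected for each patient, among them "Surgical margin, lymph node metastasis with or without capsular rupture, vascular or lymphatic embolization, perineural invasion". The sample size rests on the establishment rate alone: "To estimate the successful PDTO establishment rate, assumed around 60%, with a 95% confidence interval of 20% width, 89 tumor samples will be required".

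**The concern.** A logistic model or ROC curve fitted to a small cohort follows that cohort's noise. Its AUC, accuracy and kappa in the same patients therefore exceed what it would achieve in new ones. A similar problem arises if a continuous readout is cut at the point that best separates the observed outcomes and then tested by Chi2 on those outcomes.

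The article fixes factor-finding methods and a categorical comparison in one modest cohort, and describes the PDTO comparison as validation. A favourable result read at face value would support a stronger conclusion than this design can give. A useless factor set, or a useless PDTO score, could be reported as predictive. The primary result, the establishment rate, is not affected.

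**Working it through.** **1. The plan's own sample size.** For p = 0.60 and a 95% interval of full width 0.20, the Wilson score width is 2z·√(p(1−p)/n + z²/4n²)/(1 + z²/n). It equals 0.2006 at n = 88 and 0.1995 at n = 89, so the stated 89 is reproduced. For inclusions, 89 × 1.10 = 97.9, which gives the stated 98 ("Anticipating 10% of non-assessable samples, it is planned to include 98 patients").

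**2. Patients available for prediction.**
- Established lines: 0.60 × 89 = 53.4, about 53.
- The Background says more than two thirds of operated patients receive adjuvant treatment. At exactly two thirds, 53.4 × 2/3 = 35.6, about 36 lines.
- Clinical factors are collected for every patient, so up to 98.
- The Background says up to half relapse: at most about 26 events among 53 and 49 among 98.
- Table 2 gives about 20 baseline candidates (9 clinical, 4 histological, 3 biologic, 4 pathological). On 98 patients that is 49/20, about 2.4 events per candidate.

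**3. Apparent AUC of useless models.** Assumptions: independent normal predictors unrelated to outcome, half the patients with the event, all k factors entered in a logistic model, AUC computed in the same patients. The true AUC is 0.50.

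| Patients | 5 factors | 10 factors |
|---|---|---|
| 36 | 0.71 | 0.81 |
| 53 | 0.67 | 0.75 |
| 98 | 0.62 | 0.69 |

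**4. Adding selection (illustration).** Choose the best 5 of 20 noise candidates by AUC, then fit. At 53 patients the apparent AUC is 0.77, accuracy 75% and kappa 0.49. On new patients the AUC is 0.50. At 89 patients the apparent AUC is 0.71.

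**5. Does the correction work?** Five-fold cross-validation that repeats the selection inside each fold brings the mean AUC of these 5-of-20 models back to 0.49–0.50 at both 53 and 89 patients.

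**6. The PDTO cut, conditional on tuning.** Take one useless continuous score, cut where sensitivity plus specificity is largest on the same 53 patients, and test by uncorrected Chi2. It is significant in the hoped-for direction in about 21% of runs, with mean kappa 0.16 and accuracy 58%. At 36 patients the rate is about 18%. A median split, fixed without outcomes, gave 4 to 6% (two-sided) across sample sizes of 18, 35 and 53.

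**The case against.** The strongest reply is that much of this reads detail into a condensed article. Cut-off definition, covariate selection and internal validation are commonly left to the full protocol or the SAP, neither of which is shown. Their absence here is not an error, and this point does not rest on it.

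Three stronger readings are tempting, and the article does not support them.

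- **That ROC analysis will set the PDTO cut-off.** No sentence says so. Chi2 and kappa need categories and the readout is continuous, so some cut is implied, but its origin is open. The 20% figure is therefore conditional.
- **That the ROC and logistic models are called validated.** The word belongs to the comparison of PDTO with clinical response. The ROC and logistic sentence speaks only of identifying factors, and the objectives are secondary and cautiously worded.
- **That 20 factors will be forced into one model with about one event each.** No such model is planned. Clinical factors are available for up to 98 patients, which more than doubles the events per candidate.

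It is also fair to say that a single tuned marker would not look accurate: 58% is far below the 82% and 93% that the Background cites for a PDTO radiotherapy model. Its harm is false significance.

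What remains is that development and assessment take place in one modest cohort, that optimism persists even at 98 patients, and that the claim of validation is too strong for that design. An unseen SAP could add a correction, but it could not make a single development cohort an independent one.

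**Conclusion.** The point holds as a request to strengthen the analysis and temper the claim. It does not show that a wrong analysis has been fixed. With 5 to 10 uninformative factors, apparent AUC overstates the truth by about 0.17 to 0.25 at 53 patients (0.67 − 0.50 and 0.75 − 0.50) and by about 0.12 to 0.19 at 98. If, and only if, the PDTO cut is tuned on the same outcomes, the false-positive rate of the Chi2 test rises to about 20%.

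These sizes assume the 60% establishment rate, a binary outcome with half the patients having the event, and independent normal noise predictors. With 30% events, an assumed figure, the best-5-of-20 apparent AUC at 53 patients was 0.79 against 0.77, so the conclusion does not depend on the event share. The number of factors is also an assumption, since the article names none for the model.

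**What to change.** 1. In Statistical analyses, report AUC and calibration corrected for optimism, by bootstrap or by cross-validation that repeats any factor selection inside each resample. Apply this to a small model with factors named in advance, or to a penalised one.
2. Set the PDTO sensitive/resistant cut by any rule that does not use clinical outcomes, or analyse the readout as continuous. Which outcome-blind rule is used is a matter of preference.
3. In the section on evaluation of response to treatments, say that predictive value will be estimated, with validation left to an independent cohort.

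The cost is some wording and a few lines of code, with no new patients or data. Reported accuracy will be lower. The bootstrap correction is itself incomplete when many factors are fitted to few events, so it does not replace keeping the model small or penalised.
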